### Explanation for the choice of comparator {9b}

Participants in both the intervention and control conditions will receive VLNCs at no cost. The control condition, which does not include the message intervention, serves as a comparator to isolate the independent effects of messaging on study outcomes.

### Objectives {10}

The primary objective of the study is to examine the effect of messages about VLNCs accompanied by VLNC use (vs. use of VLNCs without messages) on the number of cigarettes smoked per day among people who smoke from three groups: those with past-month serious psychological distress (SPD), those with low SES, and those in neither category. The secondary objectives are (1) to examine the effect of messages about VLNCs in combination with VLNC use (vs. use of VLNCs without messages) on the use of other tobacco products (e.g., cigarillos, e-cigarettes), cigarette dependence, and cessation-related outcomes over the study period, and (2) to examine the effect of messages about VLNCs in combination with VLNC use (vs. use of VLNCs without messages) on perceptions and behavioral intentions.

## Methods: patient and public involvement and trial design

### Patient and public involvement {11}

There was no formal patient or public involvement in the design, conduct, or reporting of the trial. However, the team will engage with the public through (a) community partnerships and healthcare-system outreach used in recruitment, particularly to reach racially/ethnically diverse smokers with SPD and low SES, and (b) planned dissemination of findings to public health agencies, tobacco control organizations, policymakers, and the broader public.

### Trial design {12}

This randomized, open-label, controlled, multi-site study will test the efficacy of a messaging campaign about reduced nicotine cigarettes and policy in combination with the use of VLNCs. People who smoke will come from three populations: those with past-month SPD, those with low SES, and those in neither category (*n* = 262 completes for each group). Participants will complete a 1-week baseline followed by a 4-week study. They will be randomized (1:1 allocation) to either (1) the treatment condition, where VLNCs are provided during weekly visits and participants are exposed to messages about VLNCs and reduced nicotine policy, or (2) the control condition, where VLNCs without messages are provided during weekly visits. Participants can select menthol or non-menthol cigarettes based on preference. Data will be collected during in-person weekly visits and daily logs throughout the duration of the study.

Figure 1 illustrates the study design and participant progression. After screening, eligible participants will schedule a baseline visit at their preferred site, where they will complete baseline questionnaires, provide expired carbon monoxide (CO) samples, and receive a 1-week supply of the Spectrum Normal Nicotine Content Cigarettes (NNCs). One week after the baseline visit, participants will return for their randomization visit, where they will be randomly assigned into either the treatment condition (VLNCs + messages) or the control condition (VLNCs only). They will then attend 4 weekly visits over the following weeks. During each weekly visit, participants will complete questionnaires, provide an expired CO sample, and receive a 14-day supply of VLNCs (with or without the inserts, according to the assigned condition). Daily logs will be collected via text messages (sent via Twilio) with links to brief online surveys in Research Electronic Data Capture (REDCap), sent each day at a time the participant chooses, from the baseline period through week 4.

**Fig. 1 Fig1:**
[figure not shown]
Participant flow. NNCs, normal nicotine content cigarettes; VLNCs, very low nicotine content cigarettes

### Screening and baseline visit

#### Screening

Individuals interested in participation will leave their contact information on a voicemail or on a form on our website. Research staff will call each participant and describe the study in detail. After obtaining verbal consent, the participants will be asked questions over the phone to determine initial eligibility. If eligible and interested, they will be scheduled for an in-person baseline visit.

#### Baseline visit

Participants will attend their baseline visit at the study site that they select. Staff will provide a detailed study description, answer questions, finalize eligibility, and obtain written informed consent. Participants will bring packages of their usual cigarette brand to document brand preferences, complete questionnaires, and provide expired CO samples. They will receive a 1-week supply (at 150% of their normal smoking rate) of NNCs and be instructed to bring their entire supply (empty packs and unused cigarettes) to the randomization visit. Participants will be given two handouts: one graphically explaining the study flow and another explaining the use of tobacco products during the study: (1) that they are asked to only use study cigarettes; (2) if they use regular cigarettes, to report them; (3) they can use other tobacco products as they would like, but with a reminder that combusted tobacco products are the most harmful, and non-combusted less harmful, with nicotine replacement therapy (NRT) being the lowest harm. Participants who do not own a mobile phone will be given one for the duration of the study. Study personnel will explain the text messaging procedures and send a test message to the participant, who will respond and ask any questions. During the week following the baseline visit, participants will use the Spectrum NNCs and complete daily logs.

### Randomization, intervention and weekly visits

During the randomization visit (1 week after baseline), participants will be randomized into treatment (VLNCs + messages) or control (VLNCs only). Participants will be randomized using a 1:1 ratio into treatment (VLNCs + messages) or control (VLNCs only). We will use simple randomization with stratification by site, readiness to quit (planning to quit in the next 6 months vs. not), and menthol preference (menthol vs. non-menthol) with no required sample size for any of these strata. During the randomization and weekly visits, participants will complete questionnaires and provide an expired CO sample. At each visit, they will receive a 14-day supply of VLNCs (with or without the inserts, according to the assigned condition). This will ensure adequate availability of cigarettes in the different locations where participants may typically keep a supply (home, work, vehicle, etc.) as well as avoid expending the entire supply if they miss a scheduled visit. They will be instructed to return all unused cigarettes and empty cigarette packs each week; empty packs will be saved, and unused packs will be redistributed to the participants during subsequent visits. At each visit, they will see 4 messages about VLNCs (in the treatment condition) or, in the control condition, no messages. At each visit, participants will be counseled about daily log completion (based on staff review of compliance during the prior week), visit attendance, and returning unused cigarettes. Throughout the 4 weeks of the study, participants will continue to complete daily logs. During the last visit (end of week 4), participants will be referred to smokefree.gov and given a Quitline number.

### Daily logs

From the baseline period through week 4, daily logs will be collected via text messages (sent via Twilio) with links to brief online surveys in REDCap. Daily logs will assess their use of study and non-study cigarettes and other combusted and non-combusted tobacco products. Participants will report tobacco use in the past day.

## Methods: participants, interventions and outcomes

### Trial setting {13}

Recruitment and in-person visits will be administered at multiple sites: Georgia State University (PI [name]) and Emory University in partnership with Grady Memorial Hospital (Co-I [name]). Participants will be allowed to select which location they prefer for their in-person visits (GSU or Emory University; Grady Memorial Hospital is only a recruitment site). Study procedures and training will be standardized based on the protocol.

### Eligibility criteria for participants {14a}

Eligibility criteria are presented in Table 1.

**Table 1 Tab1:** Inclusion and exclusion criteria

**Inclusion**	
Age	≥ 21
Smoking status	Self-report as having smoked 100 cigarettes in their lifetime and currently smoking on 27+ days out of past 30, expired breath carbon monoxide (CO) ≥ 6 ppm [31] to assess regular smoking
Comprehension	Able to speak, read, and write in English
Availability	Available for period of study
Study cigarettes	Willingness to try novel research cigarettes
**Exclusion**	
Pregnancy	Current pregnancy or lactation; intention to become pregnant in the next 2 months
Household	Member of the same household as a study subject
Study cigarettes	Unwilling to use research cigarettes as part of the trial

### Eligibility criteria for sites and those delivering interventions {14b}

#### Sites

In-person visits are conducted at Georgia State University and Emory University (in partnership with Grady Memorial Hospital); Grady serves as a recruitment site only. Study procedures are standardized across sites per protocol.

### Individuals delivering interventions

Site PIs and project coordinators will oversee protocol adherence. All research personnel are trained in study procedures, human subjects protection, and regulatory requirements prior to site initiation. Standard operating procedures are used to ensure consistent delivery and data collection, with regular cross-site meetings for quality control.

### Who will take informed consent? {32a}

During the baseline visit, research staff at all sites will provide potential participants with a copy of the informed consent form (ICF), review the ICF in detail, and give potential participants ample time to ask questions and discuss their thoughts about possible research participation. For eligible individuals who are interested in participating, the ICF will be signed and dated by the participant and staff member. A copy of the ICF will be given to the participants.

### Additional consent provisions for collection and use of participant data and biological specimens {32b}

N/a—no biological specimens will be collected.

This study does not involve the collection, storage, or use of biological specimens. Specifically, while we will assess expired CO levels through a non-invasive breath test, no physical samples will be collected, retained, or stored. CO breath measurements are taken in real-time using a portable monitor and are recorded as numerical values only. Since no biological specimens (e.g., blood, saliva, urine, or tissue) are obtained, no additional consent provisions for biospecimen collection or use are necessary.

## Intervention and comparator

### Intervention and comparator description {15a}

#### Very low nicotine cigarettes (treatment and control conditions)

VLNCs are cigarettes with much lower levels of nicotine than normal cigarettes (possibly below addictive levels). In this study, we will use nicotine research cigarettes (NRCs) from the National Institute on Drug Abuse Drug Supply Program (NIDA DSP). Study cigarettes will be obtained from NIDA for free (NOT-DA-14-004). These will be Spectrum investigational cigarettes: regular (NRC102) and menthol (NRC103) VLNCs, which contain approximately 0.4 mg nicotine per g of tobacco. For the 1-week baseline, we will provide participants with normal nicotine cigarettes from NIDA (15.8 mg/g), regular (NRC600) or menthol (NRC601).

### Messages (treatment condition only)

Messages about VLNCs and reduced nicotine policy will be professionally developed as full-color inserts (4), still ads (4), and videos (4) in collaboration with a social marketing company using the results of our previous studies. Both general population messages and messages tailored to specific groups (people who smoke with SPD, low SES) developed in previous focus groups will be used. Messages will focus on key themes: (1) VLNCs still contain harmful chemicals and cause death and disease; (2) lower nicotine makes it easier to quit; (3) benefits of quitting smoking; 4. Reducing the nicotine level by 95% is an opportunity to quit. We will have 2 tailored messages for each priority population. For example, messages tailored for the SPD group will focus on the negative impact of smoking on anxiety, while messages for the low SES group will focus on the costs of smoking. Additional themes emerging from focus groups may also be used.

Messages will be delivered as inserts inside the packs and ads shown to the participants during the in-person study visits (4 ads at each of 5 weekly visits). Ads will be embedded in the REDCap online questionnaires and shown on a computer monitor or iPad. Pack-a-day smokers will have about 48 exposures over a 4-week study period, including exposure to 4 ads during each weekly visit (totaling 20 exposures) and daily exposure to 1 insert message (totaling 28 times). With this design, we are approximating the intensity of the real-world communication campaign.

### Criteria for discontinuing or modifying allocated intervention/comparator {15b}

At each weekly visit, participants will be asked if they have made a quit attempt in the past week.

If a participant has made a quit attempt in the past week, research staff will:Encourage the participant to continue abstaining from smoking.Schedule normal weekly visits.Provide the participant with the tobacco quitline number.Offer the option to either take home the study product or decline it. If the participant chooses to take home the study product, recommend they store the product out of sight to avoid smoking triggers.

If the participant declines the study product, instruct them to contact the research coordinator if they lapse and would like to pick up the product before the next visit.

For the safety concerns, participants will be withdrawn immediately from the study if any of the following occur:Cardiovascular disease (CVD) event: Typically includes MI (heart attack), PTCA (angioplasty/stenting), bypass surgery, stroke, peripheral vascular disease (arterial blockages in arms or legs leading to procedure or surgery). Less common CVD problems would be new cardiac arrhythmias (e.g., new atrial fibrillation) or new valvular disease (e.g., mitral or aortic regurgitation).DVT/PE (deep vein thrombosis/pulmonary embolism, i.e., blood clots in the venous system).Psychiatric Hospitalization: A subject will be withdrawn if they are hospitalized for psychiatric reasons at any time during participation in the study.Pregnancy: If subject indicates they are pregnant or have a positive pregnancy test after receipt of study products, they will be withdrawn from the study if they are continuing to use any tobacco product, and the pregnancy will be documented as an adverse event that will remain open until delivery. At that time the research staff will contact the participant to ask a few questions about the baby’s health and will update the open Adverse Event.Expired breath CO increase: A subject will be withdrawn from the study if the average of the 2 CO readings is 100 ppm or greater.

The following will be monitored and can lead to withdrawal by the PI:Expired breath CO increase: An adverse event will be documented if the average of the 2 (or 3) CO readings is:oCO is greater than 50 ppm if CO at baseline is < 20 ppm.oCO is greater than 60 ppm if CO at baseline is 20–34 ppm.oCO is greater than 70 ppm if CO at baseline 35–49 ppm.oCO is greater than 80 ppm if CO at baseline 50–64 ppm.oCO is greater than 90 ppm if CO at baseline 65–80 ppm.Changes in tobacco product use: if during the weekly visits, participants self-report a greater than 100% increase in cigarette per day (total cigarettes, including study and non-study cigarettes) relative to baseline, or a 50% increase in cigarettes per day relative to baseline that is accompanied by daily use of alternative nicotine products.Any hospitalization or debilitation in which participation in the study could be detrimental to the recovery process. This will be self-reported by the subject and will be reviewed by the PI to determine whether continued participation in the study is appropriate.If a participant is behaving in an inappropriate or threatening manner, admits to lying about eligibility criteria, including omitting previous medical diagnoses and medications, is participating in other smoking research studies that could affect the primary outcome measures, does not follow study instructions, etc., then the PI can withdraw him/her from the study at the PI’s discretion.If a participant fails to attend randomization visit, they may not be eligible to reschedule this visit or continue participation in the study without PI approval.If there is reason to believe the participant is sharing large quantities of the study product with other people.

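### A participant who becomes pregnant and has stopped tobacco stays in the trial by implication, and no stated rule prevents study cigarettes from being offered to her

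*Protocol article*

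**What the plan says.** Section {15b} of the protocol article lists pregnancy among the safety events that lead to immediate withdrawal, but attaches a condition. For a participant who reports pregnancy or tests positive after receiving study products, the rule is that "they will be withdrawn from the study if they are continuing to use any tobacco product". The pregnancy is also recorded as an adverse event and followed to delivery, when staff ask about the baby's health.

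The same section sets out what happens after quitting: "If a participant has made a quit attempt in the past week, research staff will" do several things. Among them are "Encourage the participant to continue abstaining from smoking" and "Offer the option to either take home the study product or decline it". A participant who declines is told how to obtain product after a lapse.

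The general supply rule, under Randomization, intervention and weekly visits, is that "At each visit, they will receive a 14-day supply of VLNCs". Participants return what they have not smoked each week, and "unused packs will be redistributed to the participants during subsequent visits". Trial design {12} repeats the supply rule.

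Table 1 excludes current pregnancy, lactation and intended pregnancy at entry, whatever the tobacco use.

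**The concern.** The withdrawal rule depends on tobacco use, not on the pregnancy. The pregnant participant whom it leaves in the trial is therefore the one who has stopped. She is also likely to have made a recent quit attempt, and a quit attempt is what prompts staff to offer cigarettes to take home. Staff who followed the text exactly could hand research cigarettes to an abstinent pregnant woman, and the safeguard would act only after she had smoked.

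What is at stake is her safety and that of the fetus. The protocol takes the exposure seriously: pregnancy bars entry, and any pregnancy is followed to delivery. It also recognizes that product at hand can prompt relapse, because it advises quitters who take cigarettes home to keep them out of sight.

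**Working it through.** The point concerns the wording of rules, so there is no figure in the plan to reproduce and no calculation to make. The check reads the rules in the order in which they would apply to one participant: a woman who learns that she is pregnant after randomization, tells staff, and has stopped all tobacco.

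1. **Is she withdrawn?** The condition in {15b} is continued use of any tobacco product. She does not meet it. The other items on that list (cardiovascular event, venous clot, psychiatric hospitalization, high carbon monoxide) carry no tobacco-use condition and do not describe her. No sentence says outright that she stays; this is inferred from the conditional wording.

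2. **Can the investigator withdraw her at discretion?** The second list in {15b} does not name pregnancy. Its general clauses (hospitalization or debilitation, not following instructions) might be used case by case, but none is a rule about product in pregnancy.

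3. **What do staff do about product at her next visit?** If her quit attempt fell in the past week, {15b} tells them to encourage abstinence and also says "Offer the option to either take home the study product or decline it". The instruction is not qualified for pregnancy. She may refuse.

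4. **Does a supply rule stop it?** The weekly-visit section and Trial design {12} state the supply without a pregnancy exception.

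5. **Is product already in her hands retrieved?** All participants are asked to bring unused cigarettes to each visit, but "unused packs will be redistributed to the participants during subsequent visits". The weekly return is therefore not a retrieval, and nothing in the pregnancy item adds one.

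6. **Does safety reporting stop it?** The adverse-event record and the coordinators' daily oversight in Harms {17} mean that the case would be seen. Neither says anything about withholding product.

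7. **When does protection start?** If she uses any tobacco again, study cigarettes included, and this is known, the withdrawal condition is met.

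The gap therefore runs from the time the pregnancy is known until she uses tobacco again. During it, the text permits an offer of product at a visit after a recent quit attempt, and permits her to keep product she already holds.

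**The case against.** The strongest reply is that this is a condensed article. It refers to a full protocol, standard operating procedures and a checklist for each visit, and any of these may tell staff not to dispense in pregnancy. The main safeguard is also present: no pregnant participant is permitted to go on using study product. What remains is possible possession by someone who is being encouraged to abstain and who may refuse. Every pregnancy is recorded as an adverse event, coordinators oversee safety daily, and the monitoring board reviews adverse events. A specific safety item might sensibly be read as overriding general supply text.

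Much of this stands. It limits the size of the point, and nothing here shows what staff would do in practice. It does not remove the point, because the article does more than stay silent: it states a pregnancy rule that depends on tobacco use and, in the same section, an unqualified instruction to offer cigarettes to quitters.

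A reader might infer more than the text supports:

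- *Supply by default at later abstinent visits.* This requires reading the past-week limit as ending a quitter's option to go without product. The section plainly means abstainers to be able to do so, and the strict reading would affect every quitter, pregnant or not. No count of visits should be built on it.
- *Supply after a lapse.* Those who decline are told to make contact if they relapse: staff "instruct them to contact the research coordinator if they lapse and would like to pick up the product before the next visit". But a pregnant participant who has lapsed is using tobacco again and falls under the withdrawal rule.
- *A quantity of leftover cigarettes.* Any such figure assumes that she smoked at her usual rate, whereas the case concerns someone who has stopped.
- *A contradiction with Table 1.* That table governs entry, not continuation.

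**Conclusion.** The point holds as a minor participant-safety gap. As stated, the rules keep an abstinent pregnant participant in the trial by implication and allow research cigarettes to be offered to her, or left with her, until she uses tobacco again and is withdrawn.

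The case should be rare. It needs a woman who did not intend pregnancy at entry, learns of one during a few weeks of participation, discloses it, stops all tobacco and keeps attending. The article gives no pregnancy rate, so no number of participants can be stated. Power is unaffected. So is the analysis, because section {27b} analyses all randomized participants as assigned, whatever their product use or discontinuation.

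The conclusion rests on two assumptions: that the conditional wording means what it says, so that a non-user stays in; and that no exception is given in documents not shown here.

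**What to change.** Add to the pregnancy item in {15b}: *On any report of pregnancy or positive pregnancy test, whatever the current tobacco use, no further study cigarettes will be offered, dispensed or redistributed, and unused study cigarettes will be collected. A participant who has stopped all tobacco may remain in follow-up without product.*

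Make the quit-attempt offer in {15b}, and the supply and redistribution rules in the weekly-visit section and Trial design {12}, subject to this. Keep the withdrawal of those who continue to use tobacco and the adverse-event follow-up to delivery. If an operating procedure already contains such a rule, citing it in {15b} would be enough.

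The cost is two sentences, the cross-references and a line in the visit checklist, with no added visit, procedure or participant. The downside is that a rare participant is followed without her assigned product. The protocol already accepts this for quitters who decline it, and she is still analysed in her randomized arm.

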### Outcomes {16}

#### Primary outcome

The primary outcome is the average number of cigarettes smoked per day (study and non-study cigarettes) based on 7 days’ daily logs submitted through text message prompted surveys during the last week of the trial (before the week 4 visit).

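### Withdrawal on a rise in cigarettes per day can cost the week-4 primary outcome; the daily logs should continue after the investigator acts on it

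*Protocol article*

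**What the plan says.** Section 15b of the protocol article has two tiers. For the safety events in the first tier, "participants will be withdrawn immediately from the study if any of the following occur". The second tier is discretionary: "The following will be monitored and can lead to withdrawal by the PI". It includes the case where "participants self-report a greater than 100% increase in cigarette per day (total cigarettes, including study and non-study cigarettes) relative to baseline", and also "a 50% increase in cigarettes per day relative to baseline that is accompanied by daily use of alternative nicotine products". The CPD item does not say what the person is withdrawn from. A neighbouring item in the same tier, on conduct and eligibility, does: "then the PI can withdraw him/her from the study".

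The primary outcome is the "average number of cigarettes smoked per day (study and non-study cigarettes) based on 7 days" of daily logs in the final trial week, before the week-4 visit. Section 12 has the log prompts "sent each day at a time the participant chooses, from the baseline period through week 4".

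Section 15b keeps follow-up going explicitly for one group, participants who made a quit attempt: "Schedule normal weekly visits". Section 25b mentions withdrawal only to say that people are paid for what they completed. Section 27b analyses every randomized participant in the assigned arm, including those who leave the study. Section 27c checks whether missingness is related to covariates or outcomes, uses multiple imputation under missing at random if missing completely at random is not tenable, and compares the result with a complete-data analysis.

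**The concern.** The trigger is an earlier reading of the primary-outcome variable, total CPD. If acting on it takes the person out of the study, the week-4 logs are lost for those whose smoking rose most. Participants who try to quit, whose CPD is low, are expressly kept. If the messages lower CPD, more controls than treated participants will meet the trigger. Losing the high control values then pulls the estimated difference towards zero in any analysis of observed cases only.

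Monitoring a doubling of cigarette use is reasonable, and the PI's discretion is not the issue. The issue is that the stop, as naturally read, also ends collection of an outcome that a short text-message survey could still supply.

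**Working it through.** **1. When the outcome can be lost.** The trigger is assessed at weekly visits. The week-4 logs are complete before the week-4 visit, so a rise first reported there costs nothing. Only withdrawal at visits 1 to 3 removes the outcome.

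**2. What the missingness depends on.** Withdrawal would follow CPD already reported at visits 1 to 3, plus the PI's judgement. Apart from that judgement, the outcome is missing at random given recorded data.

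**3. The plan's own numbers.** Section 19 enrols 410 per group. 410 × 0.8 = 328 randomized, and 328 × 0.8 = 262.4, stated as 262 completing. This reproduces. That is 164 per arm randomized. Losses under the trigger would fall within the planned 20% study-period attrition, so no sample size changes.

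**4. Size under assumed inputs.** The article gives no distribution for CPD, so every input here is an assumption:
- baseline CPD log-normal, median 14, log SD 0.5;
- log change from baseline with person SD 0.35 and weekly SD 0.20;
- log effect of messages −0.10;
- control log change on the very low nicotine cigarettes from −0.05 to −0.35 (section 9a says these cigarettes reduce CPD);
- trigger checked at visits 1 to 3, and analysis adjusted for baseline CPD.

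Check of scale at control change −0.05:
- Week-4 log variance = 0.25 + 0.1225 + 0.04 = 0.4125.
- Control mean = 14 × exp(−0.05 + 0.20625) = 16.37.
- Control SD = 16.37 × √(exp(0.4125) − 1) = 11.70; treated SD = 11.70 × exp(−0.10) = 10.58; pooled SD = 11.15.
- Message effect = 16.37 × (exp(−0.10) − 1) = −1.56 CPD, or 0.14 SD. This lies inside the range of 0.11 to 0.17 that section 19 gives as detectable for daily-log outcomes.

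Simulation with 1,000,000 per arm, rise above 100% only, everyone triggered withdrawn:

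| Control log change | Triggered, control v treated | Full-data difference (CPD) | Complete-case difference (CPD) | Attenuation (pooled SD) | Share of effect |
|---|---|---|---|---|---|
| −0.05 | 6.7% v 3.9% | −1.554 | −1.179 | 0.034 | 24% |
| −0.15 | 3.9% v 2.1% | −1.406 | −1.168 | 0.024 | 17% |
| −0.25 | 2.1% v 1.1% | −1.272 | −1.131 | 0.015 | 11% |
| −0.35 | 1.1% v 0.5% | −1.151 | −1.070 | 0.010 | 7% |

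First row: (1.554 − 1.179) / 11.15 = 0.034. Triggered per group: 164 × (0.0665 + 0.0386) = 17.2 at one end and 164 × (0.0111 + 0.0054) = 2.7 at the other.

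Variations:
- Half of those triggered withdrawn: 0.016, 0.011, 0.007 and 0.005 SD.
- Adding the 50% limb, assuming 20% use alternative products daily: 0.038 to 0.014 SD if all are withdrawn, 0.017 to 0.007 SD if half are.
- No true effect, rule applied evenly: at most 0.001 SD.
- Imputation using baseline and weekly CPD up to withdrawal: at most 0.002 SD.

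A separate simulation (median 13, log SD of change 0.25 to 0.45, 50% to 100% of those triggered withdrawn, message effect about 10%) gave complete-case attenuation of 0.002 to 0.037 SD, and at most 0.004 SD after imputation. With no true effect its bias was at most 0.003 SD.

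**5. Uneven discretion.** Section 24b limits blinding to hiding the hypotheses from participants. If, purely as an illustration, 25% of triggered participants were withdrawn in one arm and 75% in the other with no true effect, complete-case bias was 0.009 to 0.039 SD, in whichever direction the imbalance ran.

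**The case against.** The strongest objection is that nothing in the article says log collection ends. The CPD item does not name what the person is withdrawn from, the section heading concerns the allocated intervention, the logs run to week 4 with no stated exception, and the full protocol, which is not shown, may cover follow-up after withdrawal. This stands as a limit: loss of the week-4 logs is inferred. The inference is still the natural one. The neighbouring withdrawals are from the study, continued visits are spelled out only after quit attempts, and the one provision on withdrawn participants concerns payment.

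A reader might also infer that the outcome goes missing because of its own unseen value. The documents do not support that. The trigger uses earlier, recorded CPD, and missing at random is the assumption that section 27c makes. Imputation including weekly CPD leaves almost no bias. What remains is that section 27c brings in imputation only if missing completely at random is judged invalid, which a check may not detect with about 3 to 17 triggered participants per group. It also treats agreement with the complete-data results as supporting evidence, and that comparison stays exposed.

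A reader might further infer a serious bias or a false positive. The upper figures need a small fall in CPD on the study cigarettes, withdrawal of everyone triggered under a discretionary rule, and a complete-case analysis. With even application, the bias is towards the null when there is an effect and essentially absent when there is none.

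Finally, an automatic stop of supply for everyone who meets the trigger would be a worse rule than the present one. That is right, and the fix should not create one.

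**Conclusion.** The point holds as a cheap improvement, not as an error that threatens the trial. A stated rule allows withdrawal on an earlier reading of the primary-outcome variable and, on the natural reading, leaves a randomized participant with no observed week-4 CPD. Complete-case attenuation is roughly 0.005 to 0.04 SD in the main scenarios, and lower still if CPD varies less within persons. It is at most 0.002 to 0.004 SD with imputation on weekly CPD, and essentially zero under the null with even application. All of these sizes rest on assumed inputs, because the article gives neither the CPD distribution nor the expected frequency of triggers. Observed logs would spare the result from resting on the imputation model and would guard against uneven use of discretion in an open-label trial.

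**What to change.** Leave the trigger, the PI's discretion and all other withdrawal criteria as they are. Add to section 15b that, if the PI acts on the CPD trigger, the action is to discontinue the supply of study cigarettes, not study participation. Daily text-message logs, and the week-4 assessment where appropriate, continue unless the participant withdraws consent. Those values enter the intent-to-treat primary analysis.

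The cost is one sentence in section 15b and in the consent form, and minor follow-up for a few participants per group. Payment stays within the stated maximum: 6 visits × ($50 + $10) + 35 logs × $5 = $360 + $175 = $535. After a stop, the logs will reflect smoking off study product, and a treated participant will receive no further pack inserts. The value is valid for intent-to-treat, but it is not the same as the simulated full-data value, which assumes that supply continues.
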